
### 2.3. Outcome Measures

The intensity and magnitude of the baseline symptoms and primary (pain) and secondary (fatigue and health-related quality of life, sleep disorders, depression, physiological measures) outcome measures will be recorded by a validated Spanish version of the Brief Pain Inventory (BPI) [57] (pain intensity measure), the Patients’ Global Impression of Change (PGIC) [58] (restricted to pain intensity changes), a validated Spanish version of the revised Fibromyalgia Impact Questionnaire (FIQR) [59] (fatigue and health-related quality of life, as a secondary measure of general symptom improvement), the Pittsburgh Sleep Quality Index (PSQI) [60,61] (sleep measure), and the Beck Depression Inventory (BDI) [62,63,64,65] (depression measure). Additionally, heart rate variability (the high/low heartbeat ratio as an index of cardiac vagal regulation) and pro-inflammatory cytokine levels (TNF α, IL-1β, IL-6) will be recorded as secondary physiological outcome measures. Heart rate variability will serve as an indirect marker of the efficacy of vagal neuromodulation, at the level of its autonomic effects.

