Since fibromyalgia involves a dysregulation of the autonomic (high sympathetic tone) and immune (enhanced pro-inflammatory activity) systems [25,41], non-invasive tVNS is expected to improve the symptoms of fibromyalgia, including chronic, musculoskeletal, and generalized pain [42,43], through modulation of the vegetative and immune systems [44]. The main objective of this intervention study is to evaluate the effects of repeated sessions of tVNS on pain and other symptoms in fibromyalgia patients, comparing auricular and cervical tVNS protocols which have been probed in other pathologies [45,46,47,48,49]. According to the effectivity reported in these studies, we hypothesize that a multi-session auricular and cervical tVNS protocol carried out under safety standards will provide analgesic and therapeutic effects in fibromyalgia patients, in comparison with sham and axillary nerve stimulation controls, and secondarily will also normalize the autonomic (via heart rate variability) and immune (via pro-inflammatory cytokine levels) functions supposedly altered in this disease.

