The post-baseline outcome measures (FIQR, BPI, PGIC, PSQI, and BDI) will be recorded immediately after the fifth session of each intervention week, resulting in four intra-intervention measurements. Four additional post-intervention follow-up measures will be recorded to evaluate potential short- and long-lasting treatment effects, a week, a month, 3, and 6 months after the last intervention session, resulting in four intra-intervention and four post-intervention measurements. Although no conclusive evidence about tVNS effects on heart rate variability is available [69], heart frequency will be recorded before and after each tVNS session, the high-frequency/low-frequency heartbeat ratio will be calculated, and data will be correlated with the outcome measures. Pro-inflammatory cytokine levels taken from blood samples before the start of the intervention and immediately after 10 and 20 intervention sessions, as well as 1 week, and 1 month after the end of the intervention, will be analyzed as proposed biomarkers of the anti-inflammatory effects of the intervention [70]. To measure plasma cytokine levels, the enzyme-linked immunosorbent assay (ELISA) protocol will be used [71]. Plasma collection will be selected to optimize the yield of cytokines of interest (TNF α, IL-1β, IL-6) [72]. Within 1 h after collection, blood will be centrifuged for 10 min at 1300 g and 4 °C, and the supernatant will be transferred to a separate tube and then centrifuged for 10 min at 16,000 g and 4 °C. The resulting platelet-poor plasma will be stored in 0.5 mL aliquots at low temperatures (−80 °C) in order to maintain cytokine stability until the analysis. After each intervention, participants will be asked to guess the stimulation condition (real, sham, or unable to guess) for evaluation of successful blinding as previously reported [73], and any adverse effect of the stimulation or any aspect related to tVNS will be evaluated via an adapted standard questionnaire for assessment of adverse effects induced by a related non-invasive brain stimulation tool, namely, transcranial direct current stimulation (tDCS) [74], as a measure of the safety of the intervention. All sessions will take place at the aforementioned hospital. Figure 3 depicts the design of the study.

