### 2.6. Statistical Analysis

To exclude differences of baseline measurements (BPI scores as primary outcome measure, and FIQR, PGIC, PSQI, and BDI scores as secondary outcome measures) between groups, a mixed model 4 × 4 ANOVA will be used, with one between-group factor with four levels (4 groups), and one within-subject factor (four baseline measurements). A mixed model 4 × 8 ANOVA, with one between-group factor with four levels (four groups) and one within-subject factor (8 measurement days), will be used to analyze the scores of the outcome measures obtained in each of the questionnaires throughout the study (intra-intervention and follow-up period). In case of significant results of the ANOVAs, exploratory Bonferroni-corrected post-hoc *t*-tests will be conducted. A univariate analysis by a Chi-square test will be performed to explore the success of blinding with regard to the intervention, and *t*-tests as well as Chi-square tests will be conducted to exclude demographic differences (gender, age, and years of education) between groups. Pearson’s correlation coefficient (Pearson’s *r*) will be calculated for each tVNS group to analyze possible correlations between vagal activity measures (heart rate variability) during the intervention and questionnaire scores (FIQR, BPI, PGIC, PSQI, and BDI), as well as between pre- and post-intervention pro-inflammatory cytokines levels and outcome measures. The critical level of significance for all statistical analyses will be set to *p* < 0.05. The analyses will be carried out using the SPSS statistical software package.

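### The only named heart-rate-variability outcome is a high/low-frequency ratio, which can index autonomic balance but cannot by itself identify a vagal change; its two components should be prespecified beside it

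*Protocol article*

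**What the plan says.** Section 2.3 (Outcome Measures) of the Protocol article lists among the secondary physiological outcomes "heart rate variability (the high/low heartbeat ratio as an index of cardiac vagal regulation", and gives it a role: "Heart rate variability will serve as an indirect marker of the efficacy of vagal neuromodulation, at the level of its autonomic effects". Section 2.5 (Procedure) says how it is obtained: "heart frequency will be recorded before and after each tVNS session, the high-frequency/low-frequency heartbeat ratio will be calculated". Section 2.6 (Statistical Analysis) plans Pearson correlations in each tVNS group to look for "possible correlations between vagal activity measures (heart rate variability) during the intervention and questionnaire scores". The article names no other heart-rate-variability quantity.

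The article also limits what it claims. The outcome is secondary and is called an indirect marker. Section 2.5 concedes that the evidence for tVNS effects on heart rate variability is not conclusive. The Abstract, Introduction and Discussion all refer to the balance between sympathetic and vagal activity, and not only to vagal activity.

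**The concern.** The label and the quantity do not match. Sections 2.3 and 2.6 present the ratio as a measure of vagal function, but a ratio responds to both of its terms. If only the low-frequency term falls, the ratio rises just as it would after a rise in the high-frequency term.

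The plan's own premise makes this a live possibility. The Introduction holds that "fibromyalgia involves a dysregulation of the autonomic (high sympathetic tone) and immune (enhanced pro-inflammatory activity) systems". If the denominator stands for the other side of the balance, as the use of the ratio implies, a change confined to the denominator is a plausible result of treatment. A correlation between the ratio and pain could then come wholly from the low-frequency term and still be reported as a correlation with vagal activity. Conversely, a rise in the high-frequency term that is matched by a rise in the low-frequency term would appear as no effect. What is at stake is the mechanistic interpretation, not the efficacy result.

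**Working it through.** **The plan's own figures.** The article gives no expected value, effect size or power for heart rate variability, so there is no figure to reproduce for this outcome. Its sample-size calculation (Section 2.1) is for the BPI and does not depend on this point.

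**Inputs.** The definition R = HF/LF comes from Sections 2.3 and 2.5, with HF and LF the high- and low-frequency power. The documents give no values for HF or LF. The starting values HF = 400 and LF = 800, and all the percentage changes below, are assumptions for illustration.

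**General result.** On the log scale,

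change in log R = change in log HF − change in log LF.

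One observed number is the difference of two unknown changes, so it does not determine either. In particular, if HF is fixed and LF falls by a fraction q, R is multiplied by 1/(1 − q), a relative rise of q/(1 − q):

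- q = 0.20: 0.20/0.80 = +25%
- q = 0.50: 0.50/0.50 = +100%

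**Illustration, starting from R = 400/800 = 0.50.**

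| Assumed change | HF | LF | R | Change in R |
|---|---|---|---|---|
| LF −20%, HF unchanged | 400 | 640 | 0.625 | +25% |
| HF +25%, LF unchanged | 500 | 800 | 0.625 | +25% |
| HF +25%, LF +25% | 500 | 1000 | 0.500 | 0% |
| HF +25%, LF +50% | 500 | 1200 | 0.417 | −17% |
| HF −20%, LF −50% | 320 | 400 | 0.800 | +60% |

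The first two rows cannot be told apart from R. In the third and fourth, HF rises while R stays flat or falls. In the fifth, R rises while HF falls. The sign of the change in R therefore does not fix the sign of the change in HF. The percentage changes in R follow from the percentage changes in HF and LF alone, so they do not depend on the starting values of 400 and 800.

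**Effect on the planned correlations.** On the log scale, the covariance of log R with a questionnaire score equals the covariance of log HF with that score minus the covariance of log LF with it. A non-zero value can arise with no association at all between HF and the score.

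**The case against.** The strongest reply is that balance is one of the stated autonomic targets. If the aim is to rebalance sympathetic overactivity, a shift in the ratio driven by either term lies within the hypothesised effect. Section 2.3 also limits the marker to an indirect reading at the autonomic level. All of this stands, and it is why the ratio should be kept. It does not cover Section 2.6, where the qualifier is dropped and heart rate variability is simply called a measure of vagal activity.

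A second reply is that this is a journal article, and the full list of indices may be in a fuller document; Section 2.6 does use the plural for its measures. That excuses missing detail. It does not excuse naming one quantity in two sections and giving it a meaning that it cannot carry alone.

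A reader might infer more, and the documents do not support it:

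- *That the trial cannot detect vagal engagement at all.* The limit applies to the ratio taken alone. Its components come from the same recordings and can be analysed.
- *That 30 minutes of rest would produce a false vagal signal in the ratio.* Rest could shift high-frequency power as well, so this does not count against the ratio in particular. A shift common to all arms would not create a difference between them.
- *That the recording method is inadequate, or that a different vagal index is required.* A frequency ratio cannot be formed from a mean heart rate, so suitable recordings are implied. Such technical detail may be left out of an article, and the documents offer no basis for preferring another index.

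The documents also do not say outright that high-frequency power is the vagal term. That is implied by their placing it in the numerator of an index they call vagal.

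**Conclusion.** The point holds in a limited form. As the only named heart-rate-variability outcome, the ratio can describe sympathetic–vagal balance but does not by itself identify a vagal change, and Section 2.6 would report it as if it did. The ambiguity is not confined to small effects: a 20% fall in the low-frequency term alone mimics a 25% rise in the high-frequency term, and a 50% fall doubles the ratio. These percentages are assumed, and nothing in the documents shows how likely such changes are in these patients. The conclusion that the ratio cannot separate its terms is algebraic and does not rest on them. Calling the high-frequency term the vagal one rests on the plan's own usage.

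The consequence is confined to the interpretation of a secondary, indirect marker. The primary pain analysis and the sample size are unaffected. The change is worth making because it is nearly free and allows the trial to say which component moved.

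**What to change.** In Sections 2.3, 2.5 and 2.6:

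- Describe the high/low-frequency ratio as an index of sympathetic–vagal balance.
- Prespecify log high-frequency power and log low-frequency power, from the same recordings, as separate outcomes.
- In the Section 2.6 correlations that are described as concerning vagal activity, use log high-frequency power, and report the ratio beside it.

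Both components must already be computed to form the ratio. The cost is therefore a few changed sentences and slightly more analysis, with no added patients, visits, procedures or data. Fixing the choice in advance also prevents a choice between indices after the results are seen.

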### 2.4. Randomization Method

The tVNS effects on fibromyalgia symptoms will be evaluated in a randomized, prospective, double-blind, sham-controlled, and parallel group clinical trial, with a mixed between-group and within-group design. The data of the recruited participants will be included in a secure database, and a code per group for randomization will be generated. To allocate subjects to each group with complete randomness and independence regarding the intervention, simple randomization will be applied [66], by which the participant codes will be assigned to the respective groups via a 1:1 randomization procedure (equal allocation) [67,68] using the computer spreadsheet Microsoft Excel.

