Sample size calculation will be based on the hypothesized significant differences between (auricular vs. cervical vs. sham vs. axillary) and within (baseline vs. post-intervention) groups. We conducted an a priori calculation of the sample size by the GPower statistical power analysis tool (3.1.9.2) for a mixed-model repeated-measures ANOVA (with groups and pre/post-intervention measures as levels of the between-group and within-group factors) [50], as a primary outcome parameter conducted for the pain questionnaire (BPI). Because the main parameter of interest for this calculation is the interaction between the factors group and measure, we conducted the analysis for the within–between interaction, setting the following input parameters: effect size (f) = 0.2 (medium size), α value = 0.05, Power (1-ß) = 0.95, number of groups = 4 (pooled sham, axillary stimulation, cervical tVNS, and auricular tVNS), number of measurements = 2 (baseline as pre-intervention, and at the end of the intervention), correlation for repeated measures = 0.5, and with nonsphericity correction (1). The output parameters were: non-centrality parameter = 17.92, critical F = 2.68, actual power 0.951, and total sample size = 112. Taking into account these estimates and adding 20% to the calculated sample to compensate for possible dropouts, we will include 34 patients per group (total sample size of 136).

Written informed consent (available in Supplemental material) will be provided by all patients prior to their participation in the study. The clinical trial will be submitted for consideration and approval by the Regional Ethics Committee for Clinical Studies. In accordance with national legislation (93/42/EEC and RD 1090/2015), the study will be pre-registered in the Spanish registry of clinical studies (https://reec.aemps.es/reec/public/web.html#, accessed on 28 December 2021). The study complies with the code of Ethics of the World Medical Association Declaration of Helsinki (amend 64th, 2013).

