### 2.5. Procedure

The patients will be recruited according to the inclusion and exclusion criteria. Then, only patients without alterations in the electrocardiogram will be randomly assigned to one of five groups: auricular vagus nerve stimulation at 25 Hz frequency (atVNS) (*n* = 34); sham auricular vagus nerve stimulation (Sham atVNS) (*n* = 17); cervical vagus nerve stimulation at 25 Hz frequency (ctVNS) (*n* = 34); sham cervical vagus nerve stimulation (Sham ctVNS) (*n* = 17); axillary nerve stimulation at 25 Hz frequency (ANS) (*n* = 34). Pre-intervention baseline measures (FIQR, BPI, PSQI, and BDI) will be performed once a week for 3 weeks and before the first intervention day, resulting in four baseline measures (one per week) to evaluate the stability of the symptoms. Then, each participant will receive five 30 min consecutive sessions of stimulation (verum or sham) per week (one per day), for four weeks (in total, 20 sessions) over the left branch of the auricular or cervical vagal nerve or over the left axillary nerve, depending on the group. The patients will not be aware of the stimulation condition (verum vs. sham) within each group, and data analyses will be conducted by researchers not involved in the respective interventions, who will use numerical codes for each experimental condition in order to assure double blinding. Once the analyses have been conducted, the codes will be revealed. In the atVNS verum and sham groups, the anodal electrode will be positioned over the cymba conchae of the left auricle and the center of the left ear lobe, respectively, and the cathode (return electrode) over the antitragus. In the ctVNS verum group, the anodal electrode will be positioned on the surface of the throat that corresponds to the position of the left cervical branch of the vagus nerve, adjacent to the position of the cervical carotid artery (2 cm anterior to this branch for the sham ctVNS condition), and the cathode over the lower cheek. In the ANS verum group, the anode will be positioned over the left axillary nerve under the shoulder, and the cathode over the lower cheek. The positions of the electrodes for the respective procedures are shown in Figure 2.

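### The stated rule, simple randomisation with 1:1 equal allocation, does not match five arms fixed at 34/17/34/17/34; one allocation ratio and a restricted list should be stated

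*Protocol article*

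**What the plan says.** Three sections of the protocol article bear on allocation.

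- **Section 2.4 (Randomization Method)** fixes the method and the ratio. "simple randomization will be applied", and "the participant codes will be assigned to the respective groups via a 1:1 randomization procedure (equal allocation", using a spreadsheet.
- **Section 2.5 (Procedure)** fixes the arms. Eligible patients are "randomly assigned to one of five groups": auricular 34, "sham auricular vagus nerve stimulation (Sham atVNS) (*n* = 17", cervical 34, "sham cervical vagus nerve stimulation (Sham ctVNS) (*n* = 17", and axillary 34.
- **Section 2.1 (Participants)** fixes the size. The calculation uses four groups with the two shams pooled, and concludes: "we will include 34 patients per group (total sample size of 136".

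Section 2.6 analyses four groups. No section gives a 2:1:2:1:2 ratio, mentions blocks, or describes a two-step allocation in which sham patients are then divided between the two sham types.

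**The concern.** The conflict has two parts. The first is the ratio: 34/17/34/17/34 is 2:1:2:1:2, which is not equal allocation over five groups. The second is the method: simple randomisation assigns each patient independently, so it does not fix arm sizes, yet Section 2.5 states fixed ones.

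Two teams following this text could therefore run differently shaped trials. One would have five arms of about 27, with a pooled sham twice the size of any other group. The other would have the intended four groups of about 34. The allocation cannot be redone at the analysis stage. The comparisons that lose precision under the literal reading are the ones the Discussion stresses: the direct comparison of the two stimulation protocols, and the axillary control for specificity.

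**Working it through.** **1. The plan's own sample size (Section 2.1).** Inputs: f = 0.2, alpha = 0.05, power 0.95, g = 4 groups, m = 2 measurements, correlation 0.5, nonsphericity correction 1.

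- Noncentrality = f² × N × m / (1 − rho) = 0.04 × 112 × 2 / 0.5 = 17.92.
- Degrees of freedom: (4 − 1)(2 − 1) = 3 and (112 − 4)(2 − 1) = 108.
- Critical F = 2.689 (printed as 2.68); power = 0.9513.
- 112 × 1.2 = 134.4, taken up to 4 × 34 = 136.

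The plan's figures reproduce. They imply 112/4 = 28 per analysis group before the dropout addition and 34 after it.

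**2. The ratio in Section 2.5.** 34 + 17 + 34 + 17 + 34 = 136. Dividing by 17 gives 2:1:2:1:2. The pooled sham is 17 + 17 = 34, which agrees with Section 2.1.

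**3. Literal reading: equal allocation over five arms.**

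| Quantity | Section 2.5 | Five equal arms |
|---|---|---|
| Each verum arm, and axillary | 34 | 136/5 = 27.2 |
| Each sham arm | 17 | 27.2 |
| Pooled sham | 34 | 54.4 |

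Variance of a two-group contrast, in units of the common variance, is 1/n₁ + 1/n₂:

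- auricular vs cervical, or verum vs axillary: 2/27.2 = 0.0735 against 2/34 = 0.0588, a ratio of 1.25;
- verum vs pooled sham: 1/27.2 + 1/54.4 = 0.0551 against 0.0588, about 6% lower.

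Power of the group-by-time interaction, keeping f = 0.2 as defined for equal groups and rho = 0.5:

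| Effect pattern | 136, balanced | 136, five equal arms | 112, balanced | 112, five equal arms |
|---|---|---|---|---|
| Both verum differ from both controls | 0.981 | 0.977 | 0.951 | 0.943 |
| Only auricular differs | 0.981 | 0.959 | 0.951 | 0.912 |
| Only sham differs | 0.981 | 0.996 | 0.951 | 0.986 |

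**4. Charitable reading: four equal groups, sham halved.** This is simple randomisation with probabilities 0.25, 0.125, 0.25, 0.125 and 0.25. Expected sizes are exactly 34/17/34/17/34. The spread is binomial:

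- a 34-arm has SD √(136 × 0.25 × 0.75) = 5.05, 95% range 24 to 44;
- a 17-arm has SD √(136 × 0.125 × 0.875) = 3.86, 95% range 10 to 25;
- by simulation, the chance that at least one of the four analysis groups starts below 28 is 0.37.

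Under the literal reading the last probability is 0.95.

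**The case against.** The best defence is that the design is really a four-group one. Section 2.1 plans four groups and Section 2.6 analyses four, so 1:1 may mean equal allocation among those four, with sham divided afterwards. The expected sizes are then exactly right. This stands as a plausible intention, and it is why the figure of 27 per arm belongs to one reading only. It does not settle the text, because Section 2.5 says "randomly assigned to one of five groups" and no section describes the second step. Nor does it make simple randomisation deliver fixed sizes.

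Five stronger conclusions might be inferred, and the document does not support them.

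- **That the stated rule can never give these sizes.** It cannot be relied on to give them. On the four-group reading it gives them in expectation.
- **That the trial is underpowered.** The table shows otherwise at 136. At 112 patients on the literal reading, power falls to 0.91-0.94 in two of the three patterns. On the four-group reading, with both verum arms better than both controls, mean power is about 0.980 at 136 and 0.949 at 112.
- **That unequal sizes bias the comparison.** Chance differences in size under simple randomisation cause no bias. No planned analysis needs exact sizes, and 28 is not a validity threshold.
- **That staff see the list or fill quotas late.** The article says neither. Custody of the list is detail that an article commonly leaves to the full protocol.
- **That patients are randomised before the baseline weeks, so that run-in losses follow randomisation.** This rests only on the order of sentences in Section 2.5. The baseline sentence says only that the measures precede the first intervention day, and the design figure is not shown.

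**Conclusion.** The contradiction is real and is established from the text alone: Section 2.4 cannot be followed as written and also be expected to yield the arms of Section 2.5. Its size depends on the reading. With five equal arms, each verum arm and the axillary arm falls 20% short of 34 (27.2/34 = 0.80), and the auricular-cervical and verum-axillary contrasts have 25% more variance. With four equal groups and sham halved, the expected sizes are right and only the looseness of simple randomisation remains, which raises the variance of a two-group contrast by about 2% on average.

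These figures assume 136 patients randomised, a common outcome variance, and the plan's own f and correlation. The sample-size calculation itself is sound. This is a moderate issue of an unclear allocation rule with some loss of precision, not a failure of power or validity. It should be settled before the allocation list is generated.

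**What to change.** Reconcile Sections 2.1, 2.4 and 2.5. In Section 2.4, replace simple randomisation at 1:1 with: allocation 2:1:2:1:2 to auricular, sham auricular, cervical, sham cervical and axillary, from a pre-generated, concealed permuted-block list whose blocks sum to exactly 136. In Section 2.1, add that 34 per group refers to the four analysis groups, with sham made up of 17 + 17.

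The block total matters. Seventeen blocks of 8 (2 + 1 + 2 + 1 + 2) give 34/17/34/17/34 exactly. So does a fixed mix in random order, for example nine blocks of 8 and four of 16 (72 + 64 = 136). Block sizes drawn freely from 8 and 16 with equal chance would end exactly at 136 in only about two thirds of lists. Exact sizes also require that all 136 places are filled.

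The cost is one paragraph and a few lines of code. The small downside is some predictability at block ends for operators, who know the electrode site. Undisclosed, varied block sizes limit it, which favours the fixed mix over blocks of 8 alone.
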